**Discussion:**

The investigated patients are expected to benefit from this study, since in case of detected deviations between planned and actual treatment delivery a proper intervention (e.g., correction) could be performed in a subsequent irradiation fraction. In this way, an overall better treatment could be achieved than without any in-vivo verification. Moreover, site-specific patient-population information on the precision of the ion range at HIT might enable improvement of the CT-range calibration curve as well as safe reduction of the treatment margins to promote enhanced treatment plan conformality and dose escalation for full clinical exploitation of the promises of ion beam therapy.

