## Methods and Design

### Aims of the Study

The purpose of this clinical study is to investigate the clinical feasibility and effective benefit of off-line PET for quality assurance of scanned proton and carbon ion beam therapy for a large patient population.

The specific aims are to

1) Acquire PET/CT scan data on patients undergoing external beam ion therapy for a representative population of different tumour sites in order to be able to conclude which patients might in future benefit from PET/CT monitoring.

2) Analyze these data to determine the accuracy with which the beam range can be monitored and the actually delivered dose can be estimated.

3) Analyze these data (acquired during at least three fractions at the beginning, the middle and the end of the regular treatment course) to determine whether quantitative changes of the PET signal after delivery of the same treatment fraction dose can be indicators of physiological modifications connected to tumour response.

4) Assess the possibility of using PET/CT monitoring for quality assurance and adaptive strategies in scanned ion beam therapy.

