### Statistical Design

Feasibility and value of post-radiation PET imaging for verification of therapeutic ion beam delivery should be validated for different organ regions. Therefore, different analysis groups will be evaluated including tumors of the brain, skull base, head and neck region, upper gastrointestinal tract (upper GI), lower gastrointestinal tract (lower GI), prostate and pelvic region. For optimal calculations and verification, 30 patients per anatomic region will be analyzed. This amounts to a total patient number of 240 patients.

After acquisition of the data, correlation of the measured activity with the acquired CT imaging for patient position and anatomy will be performed. Additionally, correlation with the calculated dose plan within the Siemens Treatment Planning System (TPS) will be performed. Potential correction vectors consisting of positional changes will be determined based on the newly acquired activity images and the imaging that had been done for treatment planning.

Correlation of the measured activity level with the applied dose and pattern of RBE-values (relative biological effectiveness) determined during the biological treatment planning for particle therapy will be performed.

As activity and dose are known to be different physical quantities, an additional calculation of the expected β^+^-activity distribution will be pursued, provided that the computational tool used for this purpose is verified to deliver a corresponding calculation of dose distribution in agreement with the certified clinical TPS.

To assess whether the calculated dose and activity distribution are different from the measured activity corresponding to the applied dose distribution, a *t*-test as a one-sample location test can be used („is the difference different from zero").

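### The one test named, a one-sample t-test of zero mean difference, can screen for systematic bias but cannot answer aim 2, how accurately beam range can be monitored

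*Protocol article*

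**What the plan says.** Under Aims of the Study, the second aim is to "determine the accuracy with which the beam range can be monitored and the actually delivered dose can be estimated". Under Statistical Design, the article names one hypothesis test. Its purpose is given as "To assess whether the calculated dose and activity distribution are different from the measured activity corresponding to the applied dose distribution". The method is worded permissively: the t-test, it says, "as a one-sample location test can be used", and the question it answers is put as "is the difference different from zero".

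The other analyses in that section are correlations, for example "Correlation of the measured activity level with the applied dose and pattern of RBE-values", and the derivation of correction vectors from positional changes. None of these carries a test, a margin or a criterion of agreement.

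Just before the t-test sentence, the section gives its reason for adding a simulated activity distribution: "As activity and dose are known to be different physical quantities". That simulation is conditional, "provided that the computational tool used for this purpose is verified to deliver a corresponding calculation of dose distribution in agreement with the certified clinical" treatment planning system.

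The section sets 30 patients per anatomic region. The Study plan calls for at least three scanned fractions per patient. The abstract's Discussion adds a use in individual patients: "in case of detected deviations between planned and actual treatment delivery a proper intervention (e.g., correction) could be performed in a subsequent irradiation fraction". The abstract and the Background also say that population data on range precision might allow calibration work and smaller treatment margins.

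**The concern.** Accuracy has two parts: how far the measurements are off on average, and how much they scatter from patient to patient. Safety margins and correction of individual patients depend heavily on the second part. A test of the mean difference against zero addresses only the first, and only by asking whether an offset is detectable.

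Three consequences follow. A non-significant result may only reflect few patients or noisy measurement. Over-range and under-range errors offset each other in the mean. A significant result may concern an offset too small to matter.

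The sentence also names calculated dose as one of the things compared with measured activity. A difference between two quantities without a common unit has no natural zero.

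At stake is whether the study delivers its second aim. With only this test and uncriterioned correlations, a region with poor precision and one with good precision could both end as not significantly different from zero.

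**Working it through.** **Inputs.** From the article: n = 30 per region, a one-sample t-test, a null value of zero, at least three scans per patient. The article states no significance level, power, SD, effect size or tolerance, so it has no figure of its own on this point to reproduce. Assumed here: two-sided 5%, one signed difference per patient, a separate test per region. All values in mm are illustrative.

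**1. What non-rejection can hide.** Let d = mean bias / SD. Power = P(|T| > t(0.975; 29)), where T is noncentral t with 29 df and noncentrality d√30, and t(0.975; 29) = 2.045.

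| Bias (SD units) | Power |
|---|---|
| 0.10 | 8% |
| 0.20 | 19% |
| 0.30 | 36% |
| 0.35 | 46% |
| 0.53 | 80% |
| 0.61 | 90% |

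A bias of 0.35 SD is missed 54% of the time. With an assumed SD of 3 mm (range 2 to 4 mm), the bias detectable with 80% power is 0.53 × 3 = 1.6 mm (1.1 to 2.1 mm).

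**2. Worse precision makes rejection less likely.** Fix the bias at 1 mm and let the SD grow. The share of patients with an error above 3 mm is 1 − [Φ((3 − 1)/SD) − Φ((−3 − 1)/SD)].

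| SD (mm) | d | Test rejects | Patients off by more than 3 mm |
|---|---|---|---|
| 2 | 0.50 | 75% | 18% |
| 3 | 0.33 | 42% | 34% |
| 5 | 0.20 | 19% | 56% |
| 10 | 0.10 | 8% | 77% |

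**3. Cancellation of signed errors.** Give each patient an error of +5 or −5 mm plus noise of SD 1 mm, so that the mean absolute error is 5.0 mm.
- Sign random for each patient: rejection in 5.0% of 20,000 simulated trials, which is the nominal level.
- Exactly 15 patients each way: rejection in 0%. Here the sample SD is about √(25 × 30/29 + 1) = 5.2 mm, so the test's standard error is 5.2/√30 = 0.95 mm. The mean itself varies by only 1/√30 = 0.18 mm. A typical t is therefore about 0.2, against a critical value of 2.045.
- Errors of 3 or 10 mm give the same picture.

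If absolute differences were analysed instead, their mean would be positive by construction and a null of zero would be rejected almost automatically. That would not measure accuracy either.

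**4. Significance is not relevance.** A bias of 0.5 mm with SD 0.5 mm (d = 1) is rejected in practically every trial.

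**5. Correlation does not fill the gap.** Adding a constant range offset to every patient leaves a correlation coefficient unchanged.

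**6. Dose against activity.** One paragraph says that the two quantities differ and adds simulated activity for that reason. The next sentence lists calculated dose alongside calculated activity as things to be tested against measured activity. Read literally, the dose part has no meaningful zero. If the simulation tool is not verified, that part is all that remains.

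**7. What 30 patients can support instead.** With one value per patient:
- Mean bias: ± 2.045/√30 = ± 0.37 SD.
- SD: 95% CI from 0.80 to 1.34 times the estimate (chi-square, 29 df).
- Each 95% limit of agreement: ± 2.045 × √(1/30 + 1.96²/58) = ± 0.65 SD.
- Equivalence of the mean (two one-sided 5% tests, true difference zero): power 38%, 70%, 81%, 88% and 96% at tolerances of 0.40, 0.50, 0.55, 0.60 and 0.70 SD.

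**The case against.** The strongest reply has five parts.

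- **The test is offered, not prescribed.** The wording is permissive, this is a condensed article, and details such as limits of agreement may sit in a fuller document. This lowers the weight of the point. It does not remove it, because the article does choose a method, names no other, and the one chosen does not fit its second aim.
- **Mean bias is a proper target for part of the programme.** A systematic error in the CT-range calibration curve is a question about a mean, and a test against zero is a fair screen for it. This stands.
- **Individual deviations are not judged only through a pooled mean.** Correction vectors and interventions after detected deviations are also planned. This stands in part: neither has a stated criterion, and neither estimates accuracy.
- **The dose wording has a kinder reading.** The abstract speaks of the planned dose together with its corresponding simulated activity, so the authors may mean that dose enters only through the simulation. That is plausible, and what is needed here is clarification.
- **The mm scenarios are constructed.** They are, and they illustrate direction only. The results in SD units do not depend on them.

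A reader might go further and infer that a non-significant result will be declared proof of accuracy, or that margins will be reduced on the strength of it. The article does not support that. The test is described as looking for a difference, no verdict of accuracy is attached to it, and calibration and margin changes are mentioned only as things the population data might enable.

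**Conclusion.** The point holds in this form: the only inferential method named can flag systematic mean bias but cannot establish how accurately range can be monitored. At 30 patients per region it has 80% power only for a bias of 0.53 SD, its chance of rejecting falls as precision worsens, and it has little or no ability to see errors that offset each other (about 5% rejection with random signs, 0% with an even split). These figures assume a two-sided 5% level, one signed value per patient and a test within each region; the article states none of these. The dose-against-activity wording conflicts with the article's own statement on the two quantities and needs clarifying.

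This should be fixed but is not critical. The Background describes a pilot study, the Statistical Design section states no confirmatory hypothesis, and no margin decision is tied to the test.

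**What to change.** 1. Keep the t-test at most as a screen for mean bias, and state that a non-significant result will not be read as accuracy.
2. For the range part of aim 2, define one quantity: the per-patient difference in mm between measured and simulated activity range. For each region, report mean bias and SD with 95% CIs, and 95% limits of agreement with their CIs.
3. Handle the three or more scans within patient, for example with a random patient effect, so that between-patient and between-fraction variation are separated and scans are not counted as independent patients.
4. Claim agreement only if the intervals lie inside a tolerance that the study team states and justifies beforehand. The article gives no such figure, and none is proposed here.
5. Reword the t-test sentence so that dose enters through its simulated activity. If the simulation tool is not verified, report the comparison with dose descriptively, without a zero-difference test.

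The delivered-dose part of aim 2 is not covered by the range analysis and needs its own measure of accuracy.

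**Cost.** No new patients or scans. The team must define the range measure and set the tolerance before the analysis, which is more than a change of wording. Some regions may turn out inconclusive: at 30 patients each limit of agreement is known only to about ± 0.65 SD.

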### Ethical and legal aspects

The procedures set out in this trial protocol, pertaining to the conduct, evaluation, and documentation of this trial, are designed to ensure that all persons involved in the trial follow the guidelines of Good Clinical Practice (GCP) and the ethical principles described in the applicable version of the Declaration of Helsinki (2008 Version of the Declaration of Helsinki, adopted at the 59th WMA General Assembly, Seoul, October 2008), as well as in accordance with the „Berufsordnung für Ärztinnen und Ärzte der Landesärztekammer Baden-Württemberg"in the most recent version.

The trial will be carried out in adhering to local legal and regulatory requirements.

The study plan was submitted to the Institutional Review Board (IRB)/independent Ethics Committee (EC) of the Medical Faculty Heidelberg, and official approval was obtained.

Participation of a patient in this study is voluntary. A subject may voluntarily discontinue participation in this study at any time at their own request. Before study entry, patients will be informed by the written information brochure as well as in orally about the planned procedures within this study, especially about potential benefit for their health or potential risks. Informed consent will be documented by the patient's signature on the informed consent form.

All patients will be informed prior to initiation of study treatment concerning the aims of the study, especially with respect to any risks or side effects of the treatment, as well as the potential use of study participation for the overall treatment course. Informed consent will be documented as written informed consent by signature on the informed consent sheet. If the subject withdraws from the trial and also withdraws consent for disclosure of future information, no further evaluations should be performed, and no additional data should be collected. In all cases, the reason for withdrawal must be recorded. In case of withdrawal of a subject at his/her own request, the reason should be asked for as extensively as possible and documented. All data acquired within this study will be deleted, except if the patients allows for further evaluation of the data and inclusion into the final analysis.

The data obtained in the course of the trial will be treated pursuant to the Federal Data Protection Law (Bundesdatenschutz- bzw. Landesdatenschutzgesetz, BDSG, LDSG).

Trial findings stored on a computer will be stored in accordance with local data protection law and will be handled in strictest confidence. For protection of these data, organizational procedures are implemented to prevent distribution of data to unauthorized persons. The appropriate regulations of local data legislation will be fulfilled in its entirety.

No third party will have access to the patient data.

## Abbreviations

CT: Computer Tomography; PET: Positron-Emission-Tomography; EC: Ethics Committee; GCP: Good Clinical Practice; GSI: Gesellschaft für Schwerionenforschung; Gy: Gray; GyE: Cobalt Gray equivalent; HIT: Heidelberger Ionenstrahl Therapiezentrum; LET: linear energy transfer; LLUMC: Loma Linda University Medical Center; MGH: Massachusetts General Hospital.
